### Participant eligibility

2.3

Eligible participants will have a confirmed diagnosis of epilepsy, self‐report experiencing difficulties with their emotional health, be aged 18 years or over, and currently living in Australia.

Exclusion criteria include those who are imminently suicidal or unable to keep themselves safe, those experiencing severe cognitive difficulties with day‐to‐day memory, attention, and ability to learn basic information, those who are unable to read and understand English, or those who do not have access to the internet.

Non‐eligible applicants will be notified and strongly encouraged to speak to their primary health professional to identify local treatment options available to them. They may also be directed to the MindSpot Clinic (www.mindspot.org.au), which offers a variety of similar courses for free to all adults within Australia. A suicide risk assessment will be conducted for all participants and appropriate triaging to external community and crisis services where appropriate.

### Recruitment

2.4

The research will be promoted via advertisements/posters in newspapers, social media (e.g., Facebook, Twitter), and service providers and organizations providing services to PWE and other neurological disorders. This includes epilepsy organizations (e.g., Epilepsy Action Australia, Epilepsy Foundation, and Epilepsy Society of Australia) and hospital clinics (e.g., neurology departments). Advertisements may include placing flyers in neurology clinics and via notifications of the research on their website or social media.

These advertisements will direct participants to the eCentreClinic website (www.ecentreclinic.org) for more information. The eCentreClinic is a specialist, not‐for‐profit, research clinic that develops and evaluates online, and workbook‐delivered treatments for a range of common mental health and chronic health conditions with the aim of increasing access to effective, evidence‐based treatment.

The recruitment procedure is as follows:
Interested applicants will access a description of the study and the Participant Information and Consent Form on the eCentreClinic website. They will then elect to submit an online screening assessment, where they will complete an automated screening questionnaire to measure their symptoms and clarify that they meet the inclusion criteria.Potentially eligible participants will then be contacted by an eCentreClinic mental health clinician by telephone to complete a brief screening assessment and a structured clinical interview for DSM‐5 Mood and Anxiety Disorders (QuickSCID‐5; i.e., approx. 25 min). The purpose of this assessment is to ensure participants meet the inclusion criteria, have a complete understanding of the research, and have an opportunity to ask any questions they may have. It will also allow us to gather mental health diagnostic information for each participant, but this is not an inclusion criterion.Eligible participants will be sent an email confirming their position on the course. The email will contain a start date and information about the procedure for the first week of the course. On the first day of the course, participants are sent their login details with detailed instructions for working through the course. Participants are also provided with the contact details of the eCentreClinic Team and are invited to contact the Team via email in the event of technical issues. Participants in the guided group will be given instructions on how to contact their clinician. Thus, it is not possible to blind participants to group allocation.

### Participant safety and withdrawal

2.5

Participants are monitored regularly throughout treatment and all clinicians working with participants receive regular clinical supervision in which the progress of participants is reviewed. Serious adverse events will be reported to the HREC and eCentreClinic directors.

If a participant wishes to withdraw from the study once it has started, can do so at any time without having to give a reason. This process will be supervised by the Chief Investigator. Importantly, upon withdrawal, all participants will be provided with the option to contact the eCentreClinic Team to discuss their symptoms and other treatment services and all withdrawing participants will be encouraged to access additional services via their primary health professional.

### Procedures

2.6

The Wellbeing Neuro Course will be employed as the intervention in this study and is a digital psychological treatment for adults with neurological disorders.^31^ This intervention has been carefully developed to be suitable for adults with a broad range of neurological disorders, including PWE. It uses the principles of both cognitive behavior therapy and compensatory cognitive rehabilitation to target several domains of mental health and functional disability and covers a range of skills for managing depression, anxiety, cognitive difficulties, and activity/fatigue levels. A comprehensive overview of the intervention has been previously reported.^31^ A previous RCT of the intervention in a guided format found significant benefits on measures of depression, anxiety, disability, and cognitive function in the treatment group relative to the TAU‐WLC.^32^ Participants included a mixed sample of PWE, MS, Parkinson's disease, or an acquired brain injury. Acceptability of the treatment was also high, with over 90% of participants reporting that the course was worth their time and that they would recommend it to others.

The course includes six online lessons which are provided over a 10‐week period. Participants will work through the course according to a predetermined timetable and cannot access new materials without first having read previous materials. The course also includes worksheets for each lesson, additional written resources that can be downloaded, and case stories based on previous participants which can be followed throughout the course.

Participants allocated to the guided group will have access to support from an eCentreClinic clinician as they work through the course. All clinicians will be mental health professionals and will be employed by Macquarie University or one of its entities (e.g., MQ Health). All mental health professionals will be provided with training and supervision from a senior clinical psychologist to ensure competence and safety in their practice.

Participants in the guided group will be informed that their clinician will be available for approximately 15 min each week and will contact them throughout the course via telephone or secure messaging systems, with more time available if clinically indicated. Clinicians will be available to (1) answer questions; (2) summarize content; (3) encourage skills practice and reinforce progress; (4) enquire about participants' use of the skills; and (5) normalize challenges.

#### Randomization

2.6.1

Participants will be randomized in a ratio of 2:2:1 to guided treatment, unguided treatment, and TAU‐WLC. The rationale for the 2:2:1 randomization sequence, with smaller weighting for control participants, is related to saving recruitment resources given that previous Phase II findings demonstrate that the control group does not improve.^32^ Randomization will be performed by an independent researcher using an online randomizer (www.random.org) using permuted blocks of 10 with 2:2:1 allocation. Participants will be stratified based on referral sources. The allocation sequence will be generated prior to enrolment of the first participant and concealed from investigators until successful participant enrolment, such that the research team are unable to affect group allocation. Randomization will also be conducted such that study personnel who determine eligibility and enroll participants are blind to which treatment allocation participants will be assigned to (i.e., allocation concealment).

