### Registration and ethics

2.1

This is a intervention study conducted at one center: The eCentreClinic, School of Psychological Sciences, Macquarie University, Sydney, Australia. Participants will complete questionnaires at multiple time points. Up to 375 participants will be recruited, with recruitment planned between February 2024 and January 2027.

The project is funded by an NHMRC Medical Research Future Fund grant and additional funding support from Macquarie University. Ethics approval was granted by the Human Research Ethics Committee of Macquarie University (HREC: Reference No: 520231325151475). This trial is registered with the Australian and New Zealand Clinical Trials Registry (ANZCTR; ACTRN12623001327673).

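### A single published block size of 10, at one centre with open allocation and no stated barrier between screeners and past allocations, weakens allocation concealment more than section 2.6.1 implies

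*Protocol article*

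**What the plan says.** Section 2.6.1 (Randomization) of the protocol article fixes the ratio ("Participants will be randomized in a ratio of 2:2:1 to guided treatment, unguided treatment", with the waitlist control as the third arm) and a single block size ("using permuted blocks of 10 with 2:2:1 allocation"). It adds that "Participants will be stratified based on referral sources" and that "Randomization will be performed by an independent researcher". The sequence is made before the first enrolment and withheld until a participant has been enrolled. Staff who determine eligibility are said to be blind to the coming allocation. The stated result is a process "such that the research team are unable to affect group allocation".

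Other sections describe the setting:

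- Section 2.1 gives one centre and the planned size ("Up to 375 participants will be recruited"), with recruitment planned to January 2027.
- Section 2.4 has applicants "contacted by an eCentreClinic mental health clinician by telephone to complete a brief screening assessment", and says that participants cannot be blinded.
- Section 2.6 says that participants in the guided group "will have access to support from an eCentreClinic clinician as they work through the course".
- Section 2.3 excludes people with severe day-to-day cognitive difficulties. The article gives no cut-off for this.

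The article does not say whether the screening and guiding clinicians are different people, or whether screeners can see earlier allocations.

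**The concern.** Concealing a list protects it from being read. It does not protect it from being worked out. With one known block size, each allocation that becomes open narrows what is left in the block, and towards the end of a block some places can be known before the next applicant is assessed.

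The conditions under which this matters are present. There is a single site, arm membership is open after enrolment, and one clinic both screens and treats. Section 2.5 describes supervision in which participants' progress is reviewed, which is a plausible route for past allocations to become known. At least one exclusion, severe cognitive difficulty, leaves room for judgement as the article describes it. There is also a foreseeable motive: the Introduction suggests that people with severe or complex presentations may do poorly without clinician support.

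A screener who could foresee the next place might accept, decline or delay an applicant accordingly. That would make the arms differ at entry, and it would touch both the guided versus unguided non-inferiority comparison and the comparisons with waitlist.

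**Working it through.** **Inputs.** Block size 10, ratio 2:2:1 and stratification by referral source come from section 2.6.1; the total of 375 comes from section 2.1. The number of strata is not given. I assume that each stratum has its own blocked list. The article states no figure for predictability, so there is none to reproduce beyond the block contents: 10 × (2/5, 2/5, 1/5) = 4 : 4 : 2.

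**Observer assumed.** Someone who knows the block size, where each block starts, and every earlier allocation in the stratum. This is the worst case, so all the results below are upper bounds.

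**1. Places known with certainty.** A place is certain when only one arm remains in the block. The expected number is the sum over k of the probability that the last k places all belong to one arm:

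[C(4,k) + C(4,k) + C(2,k)] / C(10,k)

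- k = 1: 10/10 = 1
- k = 2: (6 + 6 + 1)/45 = 0.2889
- k = 3: (4 + 4 + 0)/120 = 0.0667
- k = 4: (1 + 1 + 0)/210 = 0.0095

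The sum is 1.365 per block of 10, or 13.7%. Over 375 participants, 0.1365 × 375 ≈ 51. This treats all blocks as complete; an unfinished last block in a stratum lowers it slightly.

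**2. Places known not to be waitlist.** The expected number of places after the second waitlist place is 8/(2 + 1) = 2.667 per block, or 26.7%. Over 375 this is 100.

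**3. Best guess.** The observer always names the arm with most places left. With g, u and w places left and t = g + u + w, the expected number of correct guesses is

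G(g,u,w) = max(g,u,w)/t + (g/t)·G(g−1,u,w) + (u/t)·G(g,u−1,w) + (w/t)·G(g,u,w−1)

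with G(0,0,0) = 0. This gives G(4,4,2) = 5.592, or 55.9%. Without block information, always naming one active arm is right 40% of the time.

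**4. Effect of other block schemes.** The single-size rows are exact. The mixed rows are simulated sequences of 375, with sizes equally likely and in random order, against an observer who knows the set of sizes and the full history and updates by Bayes' rule.

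| Scheme | Certain | Best guess correct |
|---|---|---|
| Fixed 10 (the plan) | 13.7% | 55.9% |
| Fixed 15 | 9.5% | 53.4% |
| Fixed 20 | 7.3% | 51.8% |
| Mixed 5/10/15 | about 3% | about 55.5% |
| Mixed 10/15/20 | about 2% | about 53% |

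Mixing sizes removes most of the certain cases. It does little to the guess rate when small blocks are in the mix. What would bring that rate back towards 40% is the observer not having the history at all.

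**The case against.** The strongest reply is that the key step is not in the documents. Sections 2.4 and 2.6 both mention clinicians of the clinic, but neither says that the same individuals screen and treat, or that screeners see past allocations. Prediction needs every earlier allocation in the stratum, including unguided and waitlist places, and the block boundaries. Stratification means that counts must be kept separately for each referral source. Section 2.6.1 also provides an independent randomizer, a list made in advance, and enrolling staff blind to what comes next. Even in the worst case, about 86% of allocations stay uncertain. Separation of staff may be set out in the full protocol.

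Most of this stands, and it limits the point: the percentages are ceilings, and access to the history is neither shown nor excluded. It does not remove the point. The safeguards protect the list and the next allocation, but they do not stop inference from allocations already open. The single block size is something that the article states, not something left out by condensing.

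Some stronger readings are tempting and are not supported:

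- **That screeners choose freely on both eligibility items.** Emotional difficulty is self-reported by the applicant, so it is not clearly a clinician's judgement.
- **That the analysis could do nothing about steering.** Baseline depression, anxiety and perceived cognition are measured, and section 3.3 plans sensitivity analyses by baseline severity. Selection on unmeasured features would remain, but the size and direction of any bias are unknown.
- **That 375 not being a multiple of 10 is a flaw.** In a single sequence of 37.5 blocks the arms finish at 148–152 : 148–152 : 74–76, and the size is given only as approximate or as a maximum.

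**Conclusion.** The point holds as a modest, conditional weakness. One published block size, at one centre with open allocations and no stated separation between screening, guiding and allocation history, leaves a minority of allocations predictable. At most 13.7% (about 51 of 375) would be certain, 26.7% (about 100) would be known not to be waitlist, and the best guess would be right 55.9% of the time instead of 40%.

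These figures assume separate blocked lists per referral source and an observer with the full stratum history. With less knowledge they fall. A reader might infer that concealment fails, or that bias has occurred. The article supports neither: concealment is weakened, and the assurance that the team cannot affect allocation is stronger than the described method can guarantee.

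**What to change.** Make two changes in section 2.6.1.

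1. For the part of each stratum's list not yet issued, have the independent researcher use randomly ordered block sizes in multiples of 5, each at 2:2:1, with the sizes and their order held only by that researcher. On the figures above, 10/15/20 does better than 5/10/15 on both measures.
2. State that staff who determine eligibility have no access to earlier allocations. This matters more for the guess rate, because varying the sizes alone leaves that rate well above 40%.

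The cost is slightly looser balance between arms at any moment, more so with larger blocks in small strata. If recruitment has begun, an amendment is needed, because regenerating unissued places departs from the statement that the whole sequence is made before the first enrolment. No extra participants are needed. The second change may need some reorganisation if the same clinicians now screen and guide.

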### Measures

2.7

A timeline of administration for the measures used is summarized in Table 1.

**TABLE 1 epi412913-tbl-0001:** Timeline for administration of measures.

Measure	Assessment	Pre‐treatment (baseline)	Weekly during treatment	Post‐treatment (10‐week treatment)	3‐month follow‐up	12‐month follow‐up
Participant measure						
Demographics	X					
QuickSCID‐5	X					
Condition details	X					
PHQ‐9	X	X		X	X	X
PHQ‐2			X			
GAD‐7	X	X		X	X	X
GAD‐2			X			
WHODAS 2.0	X	X		X	X	X
NDDIE	X	X		X	X	X
NDDIE‐suicide item			X			
BrEASI	X	X		X	X	X
NeurQol_Cognitive function		X		X	X	X
Seizure frequency	X	X	X	X	X	X
CCSQ		X		X	X	X
TSQ				X		
ReQOL‐10		X		X	X	
EQ‐5D‐5L		X		X	X	
Use of care services (purpose‐built based on the iMTA TIC‐P)		X		X	X	

Abbreviations: BrEASI, Brief Epilepsy Anxiety Instrument; CCSQ, Compensatory Cognitive Strategies Questionnaire; GAD‐7, Generalized Anxiety Disorder – 7; iMTA, Institute for Medical Technology Assessment; NDDI‐E, Neurological Depressive Disorder Inventory‐Epilepsy; PHQ‐9, Patient Health Questionnaire‐9; QuickSCID‐5, Quick Structured Clinical Interview for DSM‐5; ReQOL‐10, Recovering Quality of Life 10‐item; TIC‐P, Treatment Inventory of Costs in Patients with Psychiatric Disorders; TSQ, Treatment Satisfaction Questionnaire.

#### Psychiatric diagnostic interview

2.7.1

The Mood and Anxiety Disorders Modules of the Quick Structured Clinical Interview for DSM‐5 (QuickSCID‐5) will be administered via a telephone interview.^33^

The remaining data will be collected via online questionnaires using eCentreClinic and Macquarie University's software systems.

#### Demographic and clinical variables

2.7.2

Demographic information including gender, age, education, and employment status will be collected at the recruitment stage. Seizure frequency will also be monitored over the course of the trial.

#### Primary outcomes

2.7.3

Patient Health Questionnaire 9‐Item (PHQ‐9). This is a measure of the number and severity of symptoms of depression, based on the DSM‐IV criteria for major depressive disorder.^34^
Generalized Anxiety Disorder 7‐Item (GAD‐7). This is a measure of symptoms of anxiety, based on the DSM‐IV criteria for GAD, but is sensitive to five different anxiety disorders.^35^

#### Secondary outcomes

2.7.4

World Health Organization Disability Assessment Schedule 2.0 (WHODAS‐2). This is a 12‐item measure of disability associated with living with a chronic health condition.^36^
The Neuro‐QoL (Cognitive Function). This is a measure of perceived difficulties in cognitive abilities (e.g., attention, memory and decision‐making, or in the application of such abilities to everyday tasks (e.g., planning and remembering)).^37^
Compensatory Cognitive Strategies Questionnaire (CCSQ). This is a purpose‐built measure to assess the use of compensatory cognitive strategies before and after the intervention.^32^
Neurological Depressive Disorders Inventory‐Epilepsy (NDDI‐E). This is an epilepsy‐specific depression screener, which does not include any items that may be confounded by seizure phenomena and common side effects of medications.^38^ This will be administered as a confirmatory depression measure.Brief Epilepsy Anxiety Survey Instrument (BrEASI). This is an epilepsy‐specific anxiety screener which attempts to remove items that may be confounded by seizure phenomena.^39^ This will be administered as a confirmatory anxiety measure.

#### Quality‐of‐life and resource‐use measures

2.7.5

Recovering Quality of Life 10‐item (ReQoL‐10). This is a validated patient‐reported outcome measure used to capture mental health service users' experience of recovery in quality of life.^40^
EQ‐5D‐5L.^41^ This is a simple, preference‐based generic measure of health status used worldwide to inform cost‐utility analyses. This will be administered for validation purposes.Use of Care Services Questionnaire, a purpose‐built measure based on the Institute for Medical Technology Assessment (iMTA) Treatment Inventory of Costs in Psychiatric Patients (TIC‐P),^42^ a validated patient‐reported outcome measure to capture utilization of health services that is not captured through linked government administration data.

#### Intervention acceptability measures

2.7.6

Treatment Satisfaction Questionnaires (TSQ). This is a purpose‐built measure to assess the acceptability of online treatment courses and to measure participants' satisfaction with treatment.^32^

#### 
Substudy outcome

2.7.7

We will conduct a brief survey of referring or primary health professionals about the usefulness of the intervention and care pathway, any consequences to their patient's management, and areas for improvement.

### Data linkage

2.8

Participants will be asked to consent to have their data linked with their claims on the Medicare Benefits Schedule and Pharmaceutical Benefits Scheme and Public Hospital records to capture healthcare system costs including emergency department presentations, hospital admissions, nonadmitted care, medicines, primary care, and diagnostic services. Health record information will be obtained through the Australian Institute for Health and Welfare (AIHW), which is an Australian government service dedicated to secure linkage of health data for research purposes. The information received from AIHW will contain de‐identified data for all participants in a cohort.

### Power and sample size

2.9

Sample size was determined in line with expert guidelines^43^ and calculations included data from a previous RCT, which observed a standard rate of symptom change on our primary outcomes of depression and anxiety of 24% each.^32^ We utilized specialized longitudinal software^44^ to account for our proposed generalized estimation equations models (GEE). Power analyses were conducted with Type I error set at α = 0.05 and Type II error at β = 80% and utilized a DELTA2 methodology.^43^

Our superiority analyses will compare the two active treatment groups with the TAU‐WLC. We calculated that this requires a sample size of 125:80 (e.g., unguided: control) to detect a difference in the rate of symptom change as small as 11% on the mental health primary outcomes from baseline to post‐treatment.^44^ Our noninferiority analyses will compare the unguided and guided treatment groups. In line with power estimation for non‐inferiority thresholds^44^ in mental health trials,^45^, ^46^ we considered a difference of 50% of the standard rate of symptom reduction in depression and anxiety symptoms (i.e., 12% reduction in symptoms at post‐treatment) as the prespecified margin of noninferiority.^47^ Based on these margins, we require a sample size of 125:125 (unguided: guided).

Utilizing a conservative attrition estimate of 20%, a final larger sample of 150:150:75 (“Guided: Unguided” control) was decided.

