### Clinical efficacy

3.1

We will report clinical efficacy findings with and without data imputations under the intention‐to‐treat analysis and missing data assumptions (e.g., completer's analysis). The intention‐to‐treat approach will involve all outcomes being evaluated and imputed for all participants who were randomized and provide baseline data, consistent with previous research.^32^, ^46^

Clinical efficacy will be assessed utilizing longitudinal GEE models to assess changes in the primary and secondary clinical outcomes over time and between the three groups.

Post‐treatment is the primary endpoint for changes in the primary and secondary clinical outcomes. To determine whether post‐treatment improvements are maintained over time, within‐group time effects will be examined at 3‐ and 12‐month follow‐ups. For all analyses, the level of statistical significance will be set at alpha 0.05. All GEE models will include log‐link function and gamma scale parameters to account for the positive skew in the clinical outcome data.

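### Section 2.9 gives the Type II error as 80%, which literally means 20% power; the stated power behind both sample sizes is wrong as printed, most likely a mislabelled 80% power.

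*Protocol article*

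**What the plan says.** Section 2.9 of the protocol article sets the error rates for both sample size calculations in one sentence. It begins "Power analyses were conducted with Type I error set at α = 0.05" and continues with "Type II error at β = 80% and utilized a DELTA2 methodology".

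Two requirements follow from that sentence:

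- **Superiority of each active arm over the waiting-list control.** The plan needs 125:80 "to detect a difference in the rate of symptom change as small as 11" per cent, from baseline to post-treatment.
- **Non-inferiority of unguided to guided delivery.** The reference is an earlier trial, "which observed a standard rate of symptom change on our primary outcomes of depression and anxiety of 24% each". For the margin, "we considered a difference of 50% of the standard rate of symptom reduction in depression and anxiety symptoms", that is 12%. The requirement is 125:125.

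Section 3.1 (Clinical efficacy) returns to the significance level only: "For all analyses, the level of statistical significance will be set at alpha 0.05". It says nothing on power. Neither section says whether the 5% level is one-sided or two-sided.

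**The concern.** A Type II error is a failure to detect a difference that is there, or to establish non-inferiority when it holds. If its probability is 80%, the trial misses its target four times in five. No reader would expect a trial to be planned that way. Yet this is the only statement of planned power in the article, and it covers both the superiority comparisons and the guided-versus-unguided comparison.

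The figure matters when results are read. If superiority or non-inferiority is not shown, the first question is what chance the trial had of showing it. On the printed text the answer is 20%, and nothing elsewhere in the article tells the reader otherwise.

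**Working it through.** **Definition.** Power = 1 − β. With β = 0.80 as printed, power = 1 − 0.80 = 0.20. With β = 0.20, power = 0.80. This step needs no assumption.

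**Can the plan's own sample sizes be reproduced?** No. Section 2.9 says that longitudinal software was used to allow for the GEE models, and the article gives no standard deviation, correlation or dispersion. A condensed article may leave these out, so their absence is not a fault. It only limits the check. The question can be turned round: what standard deviation (SD) would each sample size imply at 80% power and at 20% power?

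**Inputs from section 2.9.** α = 0.05; difference 11 points with 125:80; margin 12 points (0.50 × 24) with 125:125.

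**Assumptions of this check.** A two-sample normal approximation on percentage change; two-sided 5% for superiority and the equivalent one-sided 2.5% for non-inferiority; no true difference between the arms for non-inferiority.

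**Formula.** SD = d / [(z_α + z_power) × √(1/n₁ + 1/n₂)], with z_α = 1.960 and z_power = +0.842 at 80% power or −0.842 at 20% power.

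- √(1/125 + 1/80) = √0.0205 = 0.1432
- √(1/125 + 1/125) = √0.016 = 0.1265

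| Comparison | SD at 80% power | SD at 20% power |
|---|---|---|
| Superiority, 11 points, 125:80 | 11 / (2.802 × 0.1432) = 27.4 | 11 / (1.118 × 0.1432) = 68.7 |
| Non-inferiority, 12 points, 125:125 | 12 / (2.802 × 0.1265) = 33.9 | 12 / (1.118 × 0.1265) = 84.8 |

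With a one-sided 5% level throughout (z_α = 1.645), the SDs become 30.9 and 38.2 points at 80% power, and 95.6 and 118.1 points at 20% power.

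**Reading.** In standardized terms (two-sided), the sample sizes correspond to differences of 0.40 and 0.35 SD at 80% power, or 0.16 and 0.14 SD at 20% power. If the SD is assumed to lie between 25 and 40 points, 125:80 gives 87% down to 48% power and 125:125 gives 97% down to 66%. Power as low as 20% needs an SD of about 69 to 85 points beside a mean change of 24%. The sample sizes sit more naturally with 80% power.

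**Alternative scales.**

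- *Log scale*, closer to the planned log-link gamma model: an 11-point difference is about log(1/0.89) = 0.117 to log(0.76/0.65) = 0.156. The implied log-scale SD for 125:80 is 0.29 to 0.39 at 80% power and 0.73 to 0.98 at 20% power. The direction is the same.
- *24% treated as a proportion*: a 12-point margin needs 199 per arm (one-sided 2.5%) or 157 (one-sided 5%) at 80% power, and 32 at 20% power (one-sided 2.5%). None of these is 125, so this version settles nothing.

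**What separates the two readings.** For a fixed SD, n scales with (z_α + z_power)². The ratio between 80% and 20% power is (2.802 / 1.118)² = 6.28 at two-sided 5%, or 9.58 at one-sided 5%.

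**The case against.** The strongest answer is that this is a wrong label and not a wrong calculation. 80% is a familiar power figure, the phrase reads like power with the wrong name attached, and the implied SDs point the same way. On that view, correcting it changes no sample size, margin, endpoint or analysis.

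Most of this stands. Nothing in section 2.9 shows a miscalculation. The check above is also not the trial's own calculation: it uses a two-sample normal formula in place of GEE software, and it assumes a sidedness that the article does not state.

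What does not stand is that the matter can therefore be left alone. The article has not left planned power to another document; it prints a figure, and the figure is wrong. Because it is the only one, a reader has to guess that something else was meant.

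**Conclusion.** The stated power is wrong as printed: β = 80% is 20% power, by definition, and no other statement in the article corrects it. That part rests on no assumption.

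The likeliest explanation is 80% power written as Type II error. This is an inference from the implied SDs (27 to 34 points against 69 to 85 points at two-sided 5%) under the approximation above. It cannot be confirmed from the article.

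A reader might go further and infer that the trial has only 20% power, that 125:80 and 125:125 are wrong, or that 80% power would need about 125 × 6.28 = 784 per arm. The documents do not support any of these. Each requires that 0.80 was actually used as β in the calculation, and the only hint of that is the label itself. The multiplier also changes with the sidedness, from 6.28 to 9.58.

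**What to change.** Check the stored inputs or output of both calculations in section 2.9.

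- If power was 0.80, replace the phrase with *power 80% (Type II error β = 20%)*. Nothing else changes.
- If β = 0.80 was actually used, restate the power that the planned sample gives for the 11% difference and for the 12% margin.

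The cost is a look at two stored calculations and one corrected phrase. In the second case the calculations must also be re-run, and whether the sample is still adequate would be a separate question for the sponsor once the true figure is known.
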